### Randomisation

Randomisation will be performed independently by the National Health and Medical Research Council Clinical Trials Centre, Sydney Australia (NHMRC CTC). The allocation sequence is a permuted block list consisting of blocks randomly varying between size 6 and 9. The study group allocation will be revealed to the researcher via the NHMRC CTC telephone randomisation service. No stratification factors  will be used.

### Blinding

It is not possible to blind participants in this trial given that the difference between the two interventions and the waitlist groups can be detected easily. Blinding of outcome assessors is not applicable given all assessments consist of self-report measures. Data analysts will be blinded to the group allocation of participants.

### Data management and data monitoring

Data collection will be conducted online via two digital platforms: (1) the BEeT intervention platform and (2) RedCAP, a secure electronic data capture platform. All electronic data and confidential study materials, such as participant consent forms, will be stored in an online database via the secure digital platform on which they were collected. Both platforms will only be accessible via a firewall protected website which requires a pre-authorised login and password known only to the Chief Investigator and Associate Investigators involved in data collection/analysis. The BEeT website is hosted on an isolated server, which provides complete privacy and locks the database from the public internet. Data will be de-identified and stored as an SPSS datafile on an enterprise-grade storage platform provided by the University of Sydney. Each participant will be identified in the data set by a unique numerical code. Raw data will remain available on the secure digital platform and output entered routinely into the SPSS datafile as the study progresses.

An audit of files will be conducted regularly to ensure completeness and accuracy of data collection. An independent study monitor is not appointed for this study. The trial monitoring plan is implemented by staff at the University of Sydney. Participant records are selected at random to conduct source data verification on parameters such as demographic data, key outcome variables, informed consent, indicators of risk, and adverse events. Each site will have an on-site monitoring visit at least once per year during the active phase of the study. Members of the steering committee will meet quarterly to discuss any concerns or issues which emerge from the clinical trial monitoring procedures and actions and resolutions are documented.

### Risk management

We anticipate very minimal to no risks to the participant using this intervention. However, it is possible that there may be a slight increase in psychological discomfort during or after completion of the online sessions. To monitor this, participants’ psychiatric risk status will be tracked for the duration of the trial using weekly short psychological assessments. If suicidal thoughts or self-harm is reported, a researcher will contact the participant to complete a risk assessment and provide support as required to ensure their safety. In addition, participant’s weight will be collected at two assessment points (T0 and week four) to monitor medical risks associated with rapid weight loss. If rapid weight loss is indicated, the participant will be asked to provide a weekly measure of their weight for the duration of the trial. Participants will be discontinued from the trial if their BMI is below 19. The GP will also be alerted via email if psychiatric risk rapid or weight loss is identified.

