### Trial design and setting

This study is a multisite, three-arm randomized controlled trial inclusive of two active interventions and a WLC. Participants will be recruited from the general community in Australia via advertisements on health websites and social media, referrals made from health professionals, and paper advertisements in mental health and medical clinics. If considered eligible following a screening call, the participant will be instructed to complete a standardised medical assessment with their general practitioner (GP) prior to entry to the study. After providing written informed consent, participants will be randomised to either the WLC condition or one of the intervention conditions, including pure self-help BEeT or clinician-supported BEeT. The intervention is entirely via digital modalities, including (1) *online eTherapy platform* and (2) *secure videoconferencing platform* (only for participants receiving clinician-supported BEeT). Participants randomised to the clinician-supported BEeT condition will engage in telemedicine sessions delivered by clinicians based at one of the following sites: specialist eating disorder outpatient clinic, adult community mental health team, university-based research team, and youth mental health clinic (headspace). All sites are based within New South Wales, Australia. See “Appendix A” for a list of study sites. Participants will be assessed at baseline (T0), weekly, post-intervention (T1: 12 weeks), and at 3-month follow-up (T2). The study commenced in May 2020. The study protocol has been approved by a Human Research Ethics Review Board (HREC #X18-0486). See Fig. 1 for an overview of the study process.

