### Interventions

#### Binge Eating eTherapy (BEeT)

All participants will receive access to BEeT, including both intervention conditions and WLC condition (post 10-week waitlist period). BEeT is an online self-help program that delivers the core components and strategies of CBT proven to be effective in treating eating disorders. BEeT is a 10-week program which consists of 10, one-hour interactive multimedia sessions. BEeT aims to decrease binge eating episodes and compensatory behaviours through the introduction of behavioural techniques which work to establish structured, regular eating patterns as well as cognitive techniques designed to challenge unhelpful thinking patterns related to one’s weight and appearance (See Table 1 for outline of the program components). Users are guided through the online sessions by pre-recorded videos of a therapist. Also included within the sessions are interactive activities to assist users in gaining a personalised understanding of key CBT skills. Each session becomes available every seven days, given that the previous session has been fully completed. Additionally, the program contains an inbuilt digital calendar to promote real-time self-monitoring practice via their digital device using tools such as food diary monitoring, thought challenging, feared foods exposure, and meal planning. The self-monitoring tools uphold several interactive features including a daily or weekly goal setting, scheduled reminders of goals or planned mealtimes, labelling of thoughts and emotions using animated text and images, reminders of coping skills practice, prompting questions to assist with re-framing thoughts, and a visual overview of weekly logs using colour coding to assist with recognising patterns in eating behaviours and thoughts.

**Table 1 Tab2:** Overview of binge eating etherapy session content

Session	Focus	Key principles
Session 1	Formulation and monitoring eating	Psychoeducation about cognitive-behavioural therapy Introduction to self-monitoring of eating behaviours
Session 2	Eating regularly and planning ahead	Development of personalised case formulation Psychoeducation about the role of restricting food and starvation Regular eating
Session 3	Addressing binges	Key strategies and skills to overcome binge eating and cope with urges to binge The role of triggers in the Binge Eating Cycle
Session 4	Problem solving and motivation	Problem solving Motivational enhancement strategies: pros and cons of change

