#### Waitlist control

Participants in the WLC will be offered the pure self-help BEeT intervention after a waiting period of ten weeks (T1). During the waiting period they will complete 10, brief weekly psychological assessments (approx. 5 min in length) to monitor eating disorder symptoms, psychological distress and suicidal risk.

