## Outcomes

Data will be collected via online self-report assessments. Table 2 provides an overview of assessment points and outcome measures.

**Table 2 Tab3:** Schedule of enrolment, interventions, and assessments according to SPIRIT

	TIMEPOINT**	STUDY PERIOD						
		Enrolment	Allocation	Post-allocation				
		− T_1_	0	T_0_	Weekly monitoring	T_1_	T_2_	T_3_
**Enrolment**	Eligibility screen	X						
	GP Clearance	X						
	Informed consent	X						
	Allocation		X					
**Interventions**	Clinician-supported BEeT							
	Pure self-help BEeT							
	WLC							
**Assessments**	Demographics			X				
	General mental health			X				
	Self-harm and suicidality risk assessment			X	X	X	X	X
	Eating disorder examination questionnaire (EDE-Q)			X		X	X	X
	Eating disorder examination questionnaire-short (EDE-QS)				X			
	Kessler psychological distress scale (K10)			X	X	X	X	X
	Eating disorder quality of life questionnaire (EDQOL)			X		X	X	X
	Three-factor eating questionnaire (TFEQ)			X		X	X	X
	Young schema questionnaire			X		X	X	X
	Body mass index (BMI)			X	X^1^	X	X	X
	European quality of life-5 dimensions-5 levels (ED-5D-5L)			X		X	X	X
	Evaluation of external health services utilised			X		X	X	X
	Implementation surveys					X		
	Working alliance inventory-short revised (WAI-SR)^2^					X		
	Working alliance inventory for online interventions-short form (WAI-TECH-SF)					X		

**T_0_ = baseline assessment, T_1_ = 12 week assessment (post-intervention), T_3_ = 24 week assessment (3 month follow up), T_3_ = 36 week assessment (for WLC only)

^1^BMI measured in fourth week of participation. Also measured weekly from fifth to tenth week for participants where rapid weight loss is indicated

^2^Only administered to clinician-supported BEeT participants

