### Secondary outcome measures

#### Measures of eating disorder psychopathology:

*EDE-QS* A shorter 12-item version derived from the EDE-Q, the eating disorder examination questionnaire-short (EDE-QS) assesses ED behaviours and psychopathology severity in the preceding seven days [55]. The EDE-QS is psychometrically and conceptually sound and has good reliability (Cronbach’s α = 0.90) [55, 56].

*EDQOL* The eating disorder quality of life questionnaire (EDQOL) is a disease-specific measure of health-related quality of life [57]. The EDQOL contains 25-items which assess impairment of the ED upon four primary domains: psychological, physical/cognitive, financial, and work/school. The EDQOL has good reliability (Cronbach’s α = 0.90) [57].

*TFEQ* The three factor eating questionnaire (TFEQ) is a 51-item self-report assessment which measures three dimensions of eating behaviour: cognitive restraint of eating, disinhibition/loss of control, and hunger [58]. The TFEQ has been shown to have good reliability across all three dimensions [58].

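### Unflagged self-help and waitlist participants have no scheduled trial weight from week 4 to T1 (8 weeks; 6 for waitlist if T1 is week 10), although BMI below 19 is a stop: add one at week 8

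*Protocol article*

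**What the plan says.** All places are in the protocol article.

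- *Eligibility criteria*, Box 1: entry is allowed from BMI 20. The same section has a GP sign to watch each participant's medical and psychiatric stability, at whatever intervals the GP judges suitable.
- *Discontinuation criteria* and *Risk management*: BMI below 19 is a reason to discontinue, with no limit to an arm or a time point.
- *Risk management*: "participant’s weight will be collected at two assessment points (T0 and week four"). Weekly weights follow if rapid loss is indicated, and the GP is then emailed.
- *Outcomes*, Table 2: BMI is marked at T0, in the weekly column, and at T1, T2 and T3. Footnote 1 explains the weekly mark: "BMI measured in fourth week of participation", and then "Also measured weekly from fifth to tenth week for participants where rapid weight loss is indicated".
- Timing of T1: *Trial design and setting* has "post-intervention (T1: 12 weeks"), as does the note to Table 2. *Waitlist control* says participants "will be offered the pure self-help BEeT intervention after a waiting period of ten weeks (T1").
- Next assessment: "24 week assessment (3 month follow up"). The note to Table 2 labels it T3, but it is evidently T2.
- *Clinician-supported BEeT*: a weekly weigh-in is reviewed at each telemedicine session. No such item is described for the other two arms.
- Weekly EDE-QS: it "assesses ED behaviours and psychopathology severity in the preceding seven days"; it is not listed as a weight measure.

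**The concern.** A numeric stopping rule works only when the quantity is measured. In the two arms without a clinician, the protocol schedules no weight for most of the active or waiting period after week 4, unless the participant has already been flagged. These are also the least supervised arms, and severe dietary restriction and purging are among the behaviours that qualify a person for entry.

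What is at stake is patient safety. Someone who enters near the BMI floor and begins losing weight after week 4 could pass below 19 and stay in the trial until T1 without a trial measurement showing it.

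**Working it through.** **Gaps between scheduled weights (weeks).** The documents state no figure for this, so there is none to reproduce.

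- Self-help, unflagged: weights at 0, 4, 12. Longest gap 12 − 4 = 8.
- Waitlist, unflagged: 12 − 4 = 8, or 10 − 4 = 6 if T1 is week 10.
- Supported arm, taking session n in week n: 1 at full attendance, and 12 − 10 = 2 from session 10 to T1. Two missed sessions in a row make 3, or 12 − 8 = 4 if they are sessions 9 and 10. Three in a row is discontinuation.
- With a week-8 weight: 8 − 4 = 4 and 12 − 8 = 4 (10 − 8 = 2 if T1 is week 10).

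**Margin to the stop.** (20 − 19)/20 = 5% of weight. One BMI unit in kg equals height squared: 2.40, 2.72 and 3.06 kg at 1.55, 1.65 and 1.75 m. The documents give no heights, so these are assumptions. Reaching BMI 19 exactly at T1 takes 2.40/8 = 0.30 to 3.06/8 = 0.38 kg/week over 8 weeks, or 0.40 to 0.51 kg/week over 6.

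**Illustration, not a rate.** Assume BMI 20 at week 4, steady loss from then at 0.5, 0.75 or 1.0 kg/week, and T1 at week 12.

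- Crossing week = 4 + height²/rate.
- Delay now = 12 − crossing week.
- Delay with the fix = next scheduled weight − crossing week. If a loss not yet below 19 is flagged at week 8, weekly weights run to T1.

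| Height (m) | kg/week | Crosses 19 at week | Delay now | Week-8 weight, no flag | Flagged at week 8 |
|---|---|---|---|---|---|
| 1.55 | 0.5 | 8.8 | 3.2 | 3.2 | 0.2 |
| 1.55 | 0.75 | 7.2 | 4.8 | 0.8 | 0.8 |
| 1.55 | 1.0 | 6.4 | 5.6 | 1.6 | 1.6 |
| 1.65 | 0.5 | 9.4 | 2.6 | 2.6 | 0.6 |
| 1.65 | 0.75 | 7.6 | 4.4 | 0.4 | 0.4 |
| 1.65 | 1.0 | 6.7 | 5.3 | 1.3 | 1.3 |
| 1.75 | 0.5 | 10.1 | 1.9 | 1.9 | 0.9 |
| 1.75 | 0.75 | 8.1 | 3.9 | 3.9 | 0.9 |
| 1.75 | 1.0 | 7.1 | 4.9 | 0.9 | 0.9 |

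The delay is now 1.9 to 5.6 weeks. With the fix it is 0.4 to 3.9 weeks without a flag and 0.2 to 1.6 with one. In 4 of the 9 cases (all three at 0.5 kg/week, and 1.75 m at 0.75) BMI crosses 19 after week 8, so an unflagged week-8 weight changes nothing.

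**Sensitivity to starting BMI.** From BMI 21 at 1.65 m, the loss needed is 2 × 2.72 = 5.4 kg. At 0.5 kg/week the crossing is at week 14.9, after T1; at 0.75 kg/week it is at week 11.3.

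**Waitlist after T1.** Access to BEeT is given to the "WLC condition (post 10-week waitlist period"), so the week-4 weight falls in the waiting period. Read literally, Table 2 schedules the next BMI at week 24, which is 24 − 12 = 12 weeks after T1 (14 if T1 is week 10). Weights in weeks 4 and 8 of access would fall at weeks 16, 20 and 24 (gaps of 4), or 14, 18 and 24 (longest gap 6).

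**The case against.** The strongest reply is that how often to weigh is a judgement, and that nothing in the schedule is false. There is a floor, an early check, escalation to weekly weights, a GP alert, and a weight at T1. Every participant has a GP who has agreed to monitor medical stability, and weekly symptom and risk assessments run alongside. This stands to the extent that the point is a safety improvement and not an error in a stated figure. It does not close the gap: the GP's interval is not fixed and weight is not named, and the EDE-QS is not described as measuring weight.

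Several stronger readings are tempting, and the documents do not support them.

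- A reader might infer that a loss after week 4 can never start weekly weighing. Neither *Risk management* nor footnote 1 ties the indication to the week-4 weight, so a GP report could start it.
- A reader might take the delays above as typical. They hold only for someone at BMI 20 at week 4.
- A reader might treat the 12- or 14-week waitlist interval as established. It rests partly on silence in a condensed article; the full protocol may cover monitoring during delayed access.
- A reader might see a contradiction between weekly weights for the duration of the trial (*Risk management*) and weeks 5 to 10 (footnote 1). *Risk management* describes the weekly assessments in the same terms, so it can mean the weekly monitoring period. The difference is minor.
- A reader might ask that the stop be restated for every recorded weight, including T1 and T2. The rule already has no time limit, and discontinuing people at those visits could cost follow-up data.

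**Conclusion.** The point holds as a proportionate safety recommendation. For unflagged participants in two of three arms, a stop that applies to everyone has no scheduled trial measurement behind it for 8 weeks before T1 (6 for waitlist if T1 is week 10). The gap follows directly from *Risk management* and Table 2; only the delay illustration needs assumed heights, loss rates and a BMI of 20 at week 4. A week-8 weight halves the longest pre-T1 gap to 4 weeks. For fast loss it shortens detection by itself; for slow loss the benefit depends on the rapid-loss flag at week 8. Sample size and the primary model are not affected.

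**What to change.** 1. *Risk management*: replace the sentences on weight collection with: Weight is self-reported online at T0, week 4, week 8, T1 and T2 in every arm. Where rapid loss is indicated, including at week 4 or week 8, weekly weights follow until T1.
2. Table 2, footnote 1: change to match (BMI in weeks 4 and 8; weekly until T1 where rapid loss is indicated).
3. If the full protocol does not already cover it, repeat the week-4 and week-8 items, with the same trigger, for waitlist participants during their BEeT access.
4. Let a BMI below 19 at T1 or T2 prompt a GP alert without ending outcome follow-up. The discontinuation rule needs no rewording.

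The cost is one added item in an existing weekly online assessment, two prompts for waitlist participants on BEeT if item 3 is needed, and an ethics amendment. The trial began in May 2020, so the change applies from the amendment date onward, to all arms on the same date; BMI stops can be reported by arm before and after it. The downside is slightly more weight-checking, at about the time of session 8, which works on body checking. Week 7 would also do, with gaps of 7 − 4 = 3 and 12 − 7 = 5 weeks. Routine weekly weighing in all arms is a trade-off and is not asked for.

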### Statistical methods

Initial exploratory analysis will be conducted to ensure baseline comparability between the two intervention groups and across sites. An intention to treat analysis will be conducted. Multiple imputation analysis will be implemented in accordance with missingness assumptions that fit the data (missing at random vs missing not at random), followed by a sensitivity analysis where appropriate. Generalised linear mixed modelling (GLMM) will be used to compare the effectiveness of pure self-help BEeT versus clinician-supported BEeT vs. WLC, collapsed across settings, using change in objective binge episode frequency as the primary outcome. Co-variates in the model will include baseline information of participant age, illness severity and length of illness. This will allow for assessment of the impact of participant characteristics on the key outcomes. Changes in secondary outcomes, such as psychological distress and quality of life, will also be analysed using a GLMM framework.

Time-to-event statistical methods, in particular survival analysis (cox proportional hazard modelling), will be used to examine non-compliance measures (e.g., time spent using intervention, dropout rates) and the factors impacting it (e.g., symptom severity, comorbid mental health difficulties). GLMM analysis will be used to consider the clinician-supported BEeT subgroup and factors impacting change in the EDE-Q, such as treatment setting and clinician experience to determine if the main outcome is affected by the setting in which treatment is delivered. Descriptive analysis will investigate the embeddedness and implementation of the treatment based on the clinician and the patient questionnaires.

A within-trial economic evaluation will be conducted to determine the cost-effectiveness of clinician-supported BEeT compared to pure self-help BEeT and then to the WLC from a health system perspective using individual-level data. It is crucial that the cost-effectiveness study runs alongside the clinical trial to ensure the health economic evidence is directly related to the outcomes (patient experience, clinical outcomes and quality of life) and costs of study participants (who represent an eligible population in the real world) and can immediately be used by decision-makers in the translation of results into policy and practice (including scaling-up). A cost-utility framework which expresses the main outcomes as Quality Adjusted Life Years (QALYs) will be adopted. The main hypothesis is that the Incremental Cost Effectiveness Ratios (ICERs) are favourable of clinician-supported BEeT at 12 weeks i.e. ICER < $50,000 per QALY gained. We will also assess whether the effect of clinician-supported BEeT is sustained at 3 months and re-calculate the ICERs. A utility-based and disease-generic quality of life measure, EQ-5D-5L, and a disease-specific measure, EDQOL, will be considered in the health economics analysis. Using a health system perspective, we will also be adopted to measure resource use (costs) and other benefits related to the participants and healthcare providers, including implementation costs such as clinician time costs to complete the training course and to deliver the programs. A cost questionnaire (database) will be developed specifically for this clinical trial. This questionnaire will be used to measure the type, amount and value of resources used (and hence adopting a “bottom up” costing approach). A secondary analysis will consider participants’ need for additional technologies or equipment (e.g. laptop, tablet) and time costs for completing treatment sessions. Results will be presented as ICERs which will be calculated as the difference in total costs between clinician-supported compared to pure self-help BEeT (and then compared to WLC) divided by difference in QALYS. Sensitivity analysis will be undertaken.

For the main trial analysis, data will be analysed using IBM SPSS (Version 22.0.0.0, Chicago, IL).

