Several systematic reviews have concluded that digital self-help interventions are effective in reducing eating disorder behaviours [33–40]. There is evidence to also suggest that the treatment outcomes of self-help interventions are significantly enhanced by the addition of low-intensity support from a clinician, such as a fortnightly, check-in email or phone call [12, 39, 41–43]. Supported self-help interventions only demand one-fifth of the therapist contact hours required for a complete CBT course, meaning they can be delivered in settings with low resources and capacity limits [42]. The provision of clinician support as an adjunct to self-help programs has been suggested as a viable solution to one of the most powerful critiques of digital interventions, that being the high rates of non-adherence [37, 38]. Internet-delivered CBT has the highest dropout rates of all ED treatments, ranging up to 47.2% [44]. Given the potential impact of non-adherence upon the therapeutic outcomes for patients, several reviews have highlighted the need for ongoing development and examination of novel digital treatments, with the aim of reducing the discrepancy in adherence between online platforms and more traditional modes of face-to-face treatment delivery [35, 37, 38].

Two large published studies provide evidence for the use of online CBT-based, self-help programs for individuals with BN. As part of a randomised controlled trial (RCT) conducted by Sánchez-Ortiz et al. [45] significant improvements were reported in a sample of 75 patients with full or subthreshold BN following completion of an eight-session online CBT-based program. Abstinence rates were comparable to those of patients receiving a manual-based CBT self-help intervention and face-to-face CBT program [46, 47]. Similarly, Pretorius et al. [48] observed significant reductions in BN symptomology in response to an online CBT program, supplemented with email support from a clinician and peer support via message boards, which were maintained at six-month follow up. An abridged version of BEeT has also been successfully piloted proving its acceptability, feasibility, and effectiveness in reducing core symptoms of BN [49].

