### Discontinuation criteria

Participants will be discontinued from the trial if a high level of medical or psychiatric risk is indicated. This includes severe mood instability requiring inpatient hospital admission (e.g., acute suicidality or deliberate self-harm), severe medical complications as confirmed by GP, or if the participant’s BMI drops below 19. Participants will also be discontinued if they are considered to have disengaged from the intervention evidenced by three weeks of non-completion of the online BEeT session or three consecutive missed telemedicine sessions (only for clinician-supported BEeT group).

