### Sample size

The power calculation is based on EDE-Q outcome data from a recent pilot study of BEeT [49]. The pre- to post-treatment change in objective binge episode frequency, rather than the frequency of purging was chosen as the basis for the power analysis given that not all of the participants in the current study will have engaged in purging behaviours. Accounting for multiple comparisons in the testing procedure, an alpha of 0.05 was adjusted to 0.017 under the Bonferroni method. Using a minimum of 14.9 and maximum of 23.7 for the group means (based on the findings of Barakat et al. [49]), and assuming an adjusted significance level of 0.017, a power of 0.8, and an effect size Cohen’s f = 0.3, a sample size of 48 participants is required in each of the three conditions. By applying a dropout rate of 16% (based upon findings of Barakat et al. [49]), 55 participants are needed in each group. Due to potential resourcing and time limitations, consideration was given to a worst-case scenario of sample size to be recruited. Given this, simulations of the possible impact of reduced sample size was analysed varying the parameters of an effect size (0.25–0.34) and alpha (0.01–0.025). Our worst case scenario indicates that with an effect size of 0.2, alpha of 0.017, and a sample size of 99 participants recruited, the study will have a power of 0.6. This sample size is supported by previous RCTs on eTherapies for eating disorders which have yielded very similar values in their power analyses [69–71]. The power analysis was calculated using STATA (Version 15) [72].

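### Choosing between missing at random and missing not at random by fit to the data cannot settle the primary imputation, so the plan should name one assumption in advance

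*Protocol article*

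**What the plan says.** The protocol article (Statistical methods) commits to intention to treat: "An intention to treat analysis will be conducted". Multiple imputation is then to be carried out "in accordance with missingness assumptions that fit the data (missing at random vs missing not at random), followed by a sensitivity analysis where appropriate". The same paragraph describes the main model, a generalised linear mixed model comparing the three arms "using change in objective binge episode frequency as the primary outcome". The imputation sentence therefore bears on the primary comparison. The article names no default assumption and no MNAR model.

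Three other places matter here:
- **Discontinuation criteria:** leaving the trial is tied to engagement. One trigger is "three weeks of non-completion of the online BEeT session"; another, in the clinician-supported arm only, is three consecutive missed telemedicine sessions.
- **Sample size:** the plan allows for 16% dropout and uses group means from 14.9 to 23.7.
- **Blinding:** participants are not blinded, but data analysts are.

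**The concern.** An article may leave the imputation variables or the size of an MNAR shift to an analysis plan, and that would be no fault. This sentence goes further. It states how the assumption will be chosen, and the stated method cannot make the choice. An analysis plan that follows it inherits the problem, and one that ignores it departs from the protocol.

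The choice has consequences because missing outcomes are plausibly related to outcome. People who disengage are discontinued, and people who disengage may well be doing worse. The article does not say outright whether discontinued participants are still assessed at the end of treatment. If they are not, their binge counts must be imputed, and the assumed mechanism decides what they are taken to be. The one safeguard, "followed by a sensitivity analysis where appropriate", is conditional, and nothing says it must explore departures from MAR.

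**Working it through.** **1. The plan's own figure.** A one-way analysis of variance with three groups, Cohen's f = 0.3 and alpha 0.017 gives power 0.803 at 48 per arm. The stated 48 for 80% power reproduces. No sample-size figure is disputed here.

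**2. Can fit choose between the assumptions?** Take one arm. Let p be the share observed, with mean m and SD s among those observed. Let the unobserved values have mean m + delta, so that delta = 0 is MAR (no covariates, for simplicity) and delta > 0 is MNAR with worse outcomes.
- Observed-data log-likelihood = sum of log f(y; m, s) over those observed + n_obs × log(p) + n_mis × log(1 − p). Delta does not appear.
- Arm mean = p × m + (1 − p) × (m + delta) = m + (1 − p) × delta. Delta does appear.

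Numerical check on one simulated arm of 55 with 9 missing (9/55 = 16.4%), normal with mean 14.9 and an assumed SD of 12:

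| delta | observed-data log-likelihood | estimated arm mean |
|---|---|---|
| 0 | −198.8437 | 14.08 |
| 4.4 | −198.8437 | 14.80 |
| 8.8 | −198.8437 | 15.52 |

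The fit is identical and the estimates differ. Some parametric models appear to estimate the MNAR departure, but only through distributional assumptions that the data cannot check either.

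**3. How much could it matter?**

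Inputs: group means 14.9 and 23.7 (Sample size), span 23.7 − 14.9 = 8.8; dropout 16% (Sample size).

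Assumptions, none of which the article states:
- the lower mean belongs to the active arm's completers and the higher to the waitlist;
- only active-arm dropouts are shifted;
- the imputation has no auxiliary that predicts their outcome, so it fills them at the completers' mean;
- delta runs from 0 to 8.8 episodes.

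Overstatement of the difference = dropout share × delta.
- delta = 0: overstatement 0, true difference 8.8.
- delta = 4.4: 0.16 × 4.4 = 0.70, true difference 8.8 − 0.70 = 8.10.
- delta = 8.8: 0.16 × 8.8 = 1.41, true difference 8.8 − 1.41 = 7.39.

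Cross-check of the last line: the active-arm mean is 0.84 × 14.9 + 0.16 × 23.7 = 12.516 + 3.792 = 16.308, and 23.7 − 16.308 = 7.39.

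The overstatement is proportional to dropout. At delta = 8.8 it is the same share of the span as the dropout rate, here 16%.

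**The case against.** **It is loose wording for something sensible.** The phrase could mean assumptions suited to the pattern of dropout and the reasons for it. The article does plan to study these, through Cox models of dropout (Statistical methods), platform use (Compliance) and a record of disengagement contacts (Discussion). Part of this stands: such information can make MAR more credible by improving the imputation model. It still cannot decide between MAR and MNAR, and the parenthesis presents exactly that choice.

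**MAR is itself untestable.** True, and no fault of this plan. The complaint is that no assumption is fixed in advance, not that the assumption cannot be tested.

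**A sensitivity analysis is planned.** It is mentioned, so the dependence on the assumption might still be shown. But it is conditional and its form is open.

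**The result cannot drive the method, because analysts are blinded.** A reader might infer from the unblinded participants and the data-led choice that the assumption could be picked for the arm it favours. The documents do not support that, since the Blinding section masks the data analysts. What remains is that a masked analyst also has no means of choosing by fit.

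**Dropout need not be high.** A reader might take the figure in the Introduction, "ranging up to 47.2" per cent, as what this trial expects. It is the top of a literature range for internet-delivered therapy. The plan assumes 16%, describes re-engagement contacts, and gives no dropout figure by arm.

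**Conclusion.** The point holds as a fault in a stated rule: the data cannot select the primary missing-data assumption, so the choice would be discretionary and made after data are seen. It does not show that the primary estimate will be biased.

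At the planned 16% dropout the illustrated effect is modest: at most 1.4 of 8.8 episodes within the range of delta examined. It would be less than that wherever baseline or weekly scores predict how dropouts fare, and zero if MAR holds. It is not a strict limit, since dropouts could in principle be worse than 23.7. Applying the same arithmetic to the literature maximum gives 0.472 × 8.8 = 4.2 episodes. That shows only how the effect scales with dropout and is not a forecast for this trial.

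The identifiability argument needs no assumption about this trial's data. The size rests on the assumptions listed with the calculation. The correction should be made before the data are analysed, but nothing in the design has to change.

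**What to change.** In Statistical methods, remove the clause that lets the data pick the mechanism, and the condition at the end of "followed by a sensitivity analysis where appropriate". In their place, state that:

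1. **The primary analysis assumes MAR.** Multiple imputation is done separately by arm. Auxiliaries are baseline values and the weekly EDE-QS and K10, which the schedule of assessments and the Waitlist control section place in all arms. Platform compliance data are used only in the arms that have them, because waitlist participants receive the program only after the waiting period.
2. **One MNAR sensitivity analysis is always reported.** Use delta-adjusted imputation, adding a shift to the imputed binge counts and varying it by arm. Present it as a tipping point: the shift at which the primary conclusion would change. A range from 0 to at least 8.8 episodes would cover the plan's own span of means.

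With about 55 people per arm, ten weekly assessments on two instruments would give 20 auxiliaries, so the set should be reduced in advance to a few summaries of the weekly scores.

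The cost is revised wording, a few extra imputation runs and possibly a sensitivity result less favourable to the intervention. No extra patients or data are needed.
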